### Inclusion criteria

Subjects will have to satisfy all of the following criteria to be included in the study: 1) meet the diagnostic criteria of cerebral infarction or hemorrhage; 2) meet the traditional Chinese medicine (TCM) diagnostic criteria of apoplexy; 3) had their first brain stroke with dysarthria; 4) were diagnosed with a FDA score < 27 and dysarthria combined with a ≥ b scale of pulmonary function during speech according to the FDA criteria (revised by the Rehabilitation Center of Hebei Provincial People’s Hospital; 5) are in a phase 2 weeks to 6 months after stroke; 6) have enough physical strength to complete 40-min speech training; 7) have a sitting balance ranking ≥ 3; 8) have at least normal unilateral upper-limb movement function or Brunnstrom stage of ≥ 4; 9) have normal and stable vital signs; and 10) have a willingness and ability to provide written informed consent.

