### Sample-size calculation

We anticipate that the effective rate of speech breathing-specific curative effect assessed by modified FDA will be 70 and 40% for the study and control groups, respectively. Under such an assumption, 41 participants per group (on a 1:1 ratio) will be needed to show a significant difference at a *P* value < 0.05 with a test power of 80%. Anticipating losses of 18% in follow-ups, we will establish a target sample size of 100 participants (50 participants in each group).

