### Statistical analysis

In the study, the main indicator, “speech breathing level according to modified Frenchay Dysarthria Assessment (FDA)”, will be ranked data. The statistical method will be as follows. (1) The main indicator will be compared between baseline and follow-up time with a signed rank test. The score change will be compared between groups using a rank-sum test. Unless indicated otherwise, hypothesis testing will use a two-sided test with *P* = 0.05 as the statistical cutoff point. (2) The influence of rehabilitation intervention time, stroke classification, age, and gender on the efficacy of the intervention method and the relative size of the efficacy will be estimated using a stepwise logistic regression model. (3) The overall efficacy evaluation will be the effective rate. The formula will be: Effective rate = (Excellent + Effective)/Total number of cases × 100%. A chi-squared test will be used to compare any differences in efficacy between the two groups.

The secondary outcomes will be analyzed using a repeated measure covariance analysis with the outcome baseline adjusted for as a covariate. We will test whether there is a statistically significant difference between the groups using a parameter representing treatment allocation. The ‘loudness level’ outcome is ranked data and will be analyzed in a similar way to the primary outcome.

The per-protocol (PP) population will include the randomized patients of the intention to treat (ITT) population but exclude those for whom the inclusion or exclusion criteria were not met and those who did not receive the actual treatments to which the patients were randomly allocated [18]. If the statistical results of the ITT and PP population data are the same, the results will be deemed to be reliable; if they are contrary, we intend to adopt the results of the ITT population. The method of processing missing data will be the last observation carried forward (LOCF). This refers to assigning the last observed value of the end point indicator to the subsequent missing evaluation point; that is, the last observation response will be considered to be the study end point.

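### Carrying the last observation forward as the main missing-data method can dilute the effect in a population expected to improve, and can bias the comparison in either direction if losses differ by arm

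*Protocol article*

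**What the plan says.** The Statistical analysis section fixes the rule: "The method of processing missing data will be the last observation carried forward (LOCF". It then explains that "the last observation response will be considered to be the study end point". No other missing-data method is named there. If the ITT and per-protocol results conflict, ITT prevails. The per-protocol set drops ineligible patients and those not given their allocated treatment; loss to follow-up is not a reason for exclusion.

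The Sample-size calculation section assumes that the effective rate "will be 70 and 40% for the study and control groups, respectively", and concludes that "41 participants per group (on a 1:1 ratio) will be needed to show a significant difference at a *P* value < 0.05". The stated power is 80%. On losses the section says: "Anticipating losses of 18% in follow-ups, we will establish a target sample size of 100 participants (50 participants in each group".

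The Primary outcome section schedules assessments at baseline and weeks 1, 2 and 3, and classes an unchanged grade as no response. The Inclusion criteria admit patients who "are in a phase 2 weeks to 6 months after stroke". For the other measured endpoints, "The secondary outcomes will be analyzed using a repeated measure covariance analysis", adjusted for baseline.

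**The concern.** LOCF takes a patient's status to be frozen at the last visit attended. The plan's own figures point the other way: it expects 40% of controls and 70% of LQG patients to gain at least one grade by week 3, in people at most six months from a stroke. A patient who leaves before week 1 is carried at baseline and is therefore a non-responder by definition. One who leaves after week 1 or 2 is judged on part of the training.

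The sample size and the analysis also treat losses differently. Raising 41 to 50 treats lost patients as contributing nothing, whereas the ITT analysis keeps them at an earlier score.

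Two things are at stake. If losses are alike in both arms, the estimated difference is diluted. If they differ, the carried-forward scores move the two rates by different amounts, and part of the observed difference is an artefact of who left. Unequal loss is conceivable in either direction. The Discussion expects the LQG approach to be the more acceptable one, while the section on other key points of the LQG training says that many patients cannot do the guided movements unaided (and allows for assistance). The Limitations section says that blinding was not achievable.

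For the secondary repeated-measures model, LOCF also inserts constants that are then treated as observed data, although such a model can be fitted to incomplete records directly.

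**Working it through.** **Inputs from the article.** Effective rates 0.70 and 0.40; two-sided 0.05; power 80%; 41 per arm; 18% loss; 50 per arm randomised. An effective outcome is read as a complete or partial response.

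**Inputs assumed.** The loss *d* in each arm; *f*, the share of eventual responders among the lost who already respond at their last visit (*f* = 0 means all losses fall before week 1); and loss unrelated to eventual response. The article gives no weekly trajectory, no timing of loss and no split by arm.

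**Step 1: the plan's own figure.** Pooled two-proportion formula:

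n = [1.96 × √(2 × 0.55 × 0.45) + 0.8416 × √(0.70 × 0.30 + 0.40 × 0.60)]² / 0.30² = 41.97, so 42.

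The stated 41 is within rounding of method. Power with 41 analysed per arm is 79.0% (exact uncorrected chi-squared 81.3%). Inflation: 41 / (1 − 0.18) = 50, as stated. So 79% (exact 81%) is the benchmark. The 86.6% obtained with 50 per arm and no loss is not the planned power.

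**Step 2: equal loss.** Rate seen under LOCF = p × [1 − d(1 − f)]. With d = 0.18 this is p × (0.82 + 0.18f). Power at n = 50 per arm is Φ{[Δ√n − 1.96√(2p̄q̄)] / √(p₁q₁ + p₂q₂)}.

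| f | LQG | Control | Difference (points) | Power, normal | Power, exact |
|---|---|---|---|---|---|
| 0 | 57.4% | 32.8% | 24.6 | 70.1% | 72.1% |
| 1/3 | 61.6% | 35.2% | 26.4 | 76.0% | 78.0% |
| 1/2 | 63.7% | 36.4% | 27.3 | 78.8% | 80.7% |
| 2/3 | 65.8% | 37.6% | 28.2 | 81.5% | 83.2% |
| 1 | 70.0% | 40.0% | 30.0 | 86.6% | 87.6% |

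With no true effect, equal loss leaves the exact type I error at 4.9% to 5.7% for common rates of 40%, 55% and 70%.

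**Step 3: unequal loss with the planned effect (f = 0).**
- 26% LQG, 10% control: 0.70 × 0.74 = 51.8% against 0.40 × 0.90 = 36.0%. The difference is 15.8 points and power 35% (exact 37%).
- 10% LQG, 26% control: 0.70 × 0.90 = 63.0% against 0.40 × 0.74 = 29.6%. The difference is inflated to 33.4 points.

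**Step 4: unequal loss with no true effect.** True response 55% in both arms, splits averaging 18%, exact chi-squared with 50 per arm:

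| Loss in the two arms | f = 0 | f = 1/3 | f = 1/2 |
|---|---|---|---|
| 18% / 18% | 6% | 6% | 6% |
| 15% / 21% | 7% | 6% | 6% |
| 14% / 22% | 8% | 7% | 6% |
| 12% / 24% | 11% | 8% | 7% |
| 10% / 26% | 15% | 10% | 8% |
| 9% / 27% | 18% | 11% | 9% |

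For example, at 10%/26% and f = 0 the seen rates are 0.55 × 0.90 = 49.5% and 0.55 × 0.74 = 40.7%, a false difference of 8.8 points.

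These figures are for the effective rate. The rank-sum test of score change uses the same carried-forward grades, but its loss of power was not computed.

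**The case against.** The strongest reply is that the damage is modest in the middle cases. Against the planned 79%, the nine extra patients per arm roughly offset the dilution: 76% at f = 1/3, 79% at f = 1/2, and above plan from f = 2/3. The 70% figure needs every loss to fall before week 1, and type I error of 11% or more needs a marked imbalance such as 12%/24% or 9%/27%. The article supports neither, and with milder splits the error is 6-8%. All of this stands, and it is why the sizes are given as ranges.

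A reader might also infer three stronger things that the article does not support:
- That all early losses count as failures. Only losses before week 1 do so by rule; weeks 1 and 2 are assessed, so a later loss can carry a response forward.
- That LOCF always shrinks the effect and is therefore conservative. Heavier control loss exaggerates it.
- That the primary tests have wrong standard errors. The rank-sum and chi-squared tests use one value per patient, and the chi-squared test keeps about 5-6% error under equal loss. Treating constants as observed data is a problem for the secondary repeated-measures model, and no size is computed for it.

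It is fair, too, that sensitivity analyses may sit in a full protocol or analysis plan not shown, so their absence is not held against the article. The point rests on LOCF being stated as the method. Finally, a missing-at-random analysis has its own weakness: for a patient lost before week 1 it has only the baseline grade to work from.

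**Conclusion.** The point holds as a should-fix. LOCF is a stated choice that does not fit patients whom the plan itself expects to improve, and the sample size does not reflect it. Equal 18% loss dilutes the 30-point difference to between 24.6 points (worst case) and 27.3 points (f = 1/2), with power from 70% (exact 72%) to 79% (exact 81%) against a planned 79% (exact 81%), and without raising the false-positive rate. If most lost responders already respond when lost, power is at or above plan. Unequal loss is the more serious risk, because it biases the comparison and its direction cannot be known in advance: heavier LQG loss hides an effect and heavier control loss exaggerates it. The ITT and per-protocol comparison would not reveal this, since lost patients are not excluded as such from either set.

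All sizes depend on assumed timing and arm split and on loss being unrelated to eventual response. A claim that power will be 70%, or that type I error will reach 18%, goes beyond the document.

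**What to change.** Replace LOCF as the main method, before any unblinded data are analysed.

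- **Speech-breathing grade and effective rate at week 3:** multiple imputation by arm from the baseline, week-1 and week-2 grades, keeping the planned rank-sum and chi-squared comparisons; or an ordinal repeated-measures model.
- **Measured secondary outcomes:** a mixed model for repeated measures on observed data, with baseline and treatment-by-visit terms and no imputation.
- **Sensitivity:** keep LOCF here, together with an analysis that departs from missing-at-random separately by arm.
- **Reporting:** show losses by arm and week, so that readers can see which scenario applied.

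The cost is analysis-plan wording and a little more programming. No new visits are needed, because weekly scores are already collected. The downside is reliance on a stated missing-at-random assumption, which is weakest for patients lost before week 1; the by-arm departure analysis is there to test it.

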#### Trial quality control

The evaluation will be handled by a person in charge to establish unified evaluation and operation procedures.

#### Researcher training

Prior to the beginning of the project, the participating physicians will undergo unified training. Through training, the researchers will fully understand the purpose, plans, indicators, and the Case Report Form (CRF) filing of the clinical research program and will be required to adhere to the study concept. Each physician will have a “researcher’s manual” for easy reference.

## Discussion

Six Character Formula or *LQG* is one of the common forms of Chinese qigong focused on breath control through inhalation and exhalation of six sounds with a history of more than 1500 years. The exercises feature slow and gentle movement of the mouth and tongue, which is believed to regulate the rise and fall of qi (vital energy) through the meridian system in the body and to help nourish the corresponding organs [19, 20]. Since patients with dysarthria retain basic language ability but have muscular dysfunctions in controlling articulation, respiration, phonation, prosody, and resonation [21], we hypothesize that post-stroke dysarthria patients will overcome speech difficulties by practicing *LQG* to increase breathing control abilities, strengthening face and mouth musculature, and improving the movement of the mouth and tongue. We expect that *LQG* will result in gradual transition from costal breathing to abdominal breathing through guidance of limb movements and the combination of both articulation and mouth shape. Such breathing training is expected to be more acceptable by patients and will promote maximum recovery of their breathing coordination. Therefore, the current study is designed to compare the therapeutic effect of the Six Character Formula vs traditional breathing training in patients with post-stroke dysarthria complicated by abnormal breath control. There are six types of dysarthrias, including spastic, flaccid, ataxic, hyperkinetic, hypokinetic, and mixed [22–24], and each condition is characterized by a different etiology and different speech behaviors, as well as different levels of respiratory control abnormalities. FDA [25] is one of the formal assessment tools used to obtain a complete oral-facial examination and a method to identify the primary speech characteristics, which can contribute to the neurological diagnosis and treatment guidance. Patients with post-stroke dysarthria and simultaneous abnormal respiratory control will be selected as our study subjects through a modified FDA. Modified FDA and other examinations, including MCA, S/Z ratio, and loudness scale, will be conducted in the current study to comprehensively evaluate the therapeutic effects of the training therapies.

In summary, the proposed study will focus on dysarthria complicated by abnormal breathing control and intends to introduce *LQG* into post-stroke dysarthria rehabilitation by highlighting the breath–speech synchronous training exercise.

### Limitations of the study

The limitations of the study include the following: (1) due to the limited medical resources and the short hospitalization period, the intervention period for this study will only be 3 weeks; (2) the subjects will not be followed-up after intervention; (3) we cannot realistically achieve single-blind or double-blind conditions, which is a limitation of research on rehabilitation therapy; (4) the evaluation index is mainly subjective and objective—quantitative indicators will need to be added in future research.

### Trial status

#### Ongoing trial

We have not completed patient recruitment at the time of submission.

## Abbreviations

COPD: Chronic obstructive pulmonary diseases
CR: Complete response
FDA: Frenchay Dysarthria Assessment
HRV: Heart rate variability
*LQG*: *Liuzijue qigong*
LSVT: Lee Silverman voice treatment
MCA: Maximal counting ability
MPT: Maximum phonation time
NR: No response
NSOMExs: Non-speech oro-motor exercises
PD: Parkinson’s disease
PR: Partial response
S/Z ratio: Signal–noise ratio
TCM: Traditional Chinese medicine
